## Adverse Events

The treating investigator or qualified designee will assess each subject to evaluate for potential new or worsening AEs as specified in the Study Calendar (section 15) or more frequently if clinically indicated. Please refer to Section 14 for detailed information regarding the assessment and recording and reporting of AEs.

## Full Physical Exam

The treating investigator or qualified designee will perform a full physical exam during the screening period. Clinically significant abnormal findings should be recorded as medical history. Full physical exam requires assessment of major organ sites (Constitutional, Head and Neck, Cardiovascular, Pulmonary, Abdominal, Musculoskeletal, Lymph, Neurological, and Skin).

## Focused Physical Exam

Except for at screening, the treating investigator or qualified designee will perform a focused abdominal and pelvic genitourinary physical exam during the baseline visit and at each follow-up visit post-operatively if clinically indicated.

## Vital Signs

The treating investigator or qualified designee will take vital signs at screening. Vital signs should include: temperature, pulse, respiratory rate, height, weight and blood pressure.

## Eastern Cooperative Oncology Group (ECOG) Performance Scale

The treating investigator or qualified designee will assess ECOG status **(see Appendix A)** at screening.

## Assessment of Disease

Only the treating investigator or qualified designee (MD only) may determine the assessment of disease recurrence or response. Response evaluation will be based on the I-PSS, the SHIM and the EPIC-26, and based upon the subject’s post-FT 6-month mpMRI & MRI-TB.

## Laboratory Safety Evaluations (Hematology, Chemistry and Urinalysis)

Laboratory tests for hematology, chemistry, and others are specified in Table 5 and should be performed at the timepoints specified in the study calendar.

**Table 5. Laboratory Tests**

| **Hematology** | **Chemistry** | **Other** |
| --- | --- | --- |
| Hematocrit | Albumin | PSA |
| Hemoglobin | Alkaline phosphatase | Testosterone |
| Platelet count | Alanine aminotransferase (ALT) |  |
| WBC (total and differential) | Aspartate aminotransferase (AST) |  |
| Red Blood Cell Count | CO_2_ or bicarbonate |  |
| Absolute Neutrophil Count | Calcium |  |
| Absolute Lymphocyte Count | Chloride |  |
| Absolute Eosinophil Count | Glucose |  |
|  | Blood Urea Nitrogen |  |
|  | Potassium |  |
|  | Sodium |  |
|  | Creatinine |  |
|  | Total protein |  |
|  | Total Bilirubin |  |
|  | Direct Bilirubin (If total bilirubin is elevated above the upper limit of normal) |  |

# STATISTICAL CONSIDERATIONS

## Study Design/Endpoints

This study will be a multi-institutional single arm phase I/II trial with a recruitment goal of 57 patients with treatment naïve non-metastatic intermediate-risk PCa.

Primary endpoints

1. To determine the proportion of men with CSPCa (GG ≥2) in the ablated prostate tissue by performing a surveillance mpMRI and MRI-TB at 12-months following FT.
2. To determine the proportion of men with CSPCa (GG ≥2) in the unablated prostate tissue by performing a surveillance mpMRI and MRI-TB at 12-months following FT.
3. To demonstrate the safety of combining ADT, and FT for the treatment of men with histopathologic diagnosis of GG 2 & 3 PCa, with PSA level < 20 ng/mL utilizing the NCI’s CTCAE v.5 classification to quantify and characterize the incidence of AEs.

Secondary endpoints

1. To define change in genitourinary and sexual function from baseline following ADT, and FT by measuring the subject’s HRQoL (I-PSS, SHIM, EPIC-26) at 6-and 12-months after FT.
2. To determine the PSA response to the combination treatment by measuring the subject’s PSA at “baseline” (PSA at time of initial diagnosis) and then at 3-months, 6-months, and 1-year from FT.
3. To determine the proportion of men converting to whole gland therapy (radical prostatectomy or radiation therapy) and/or requiring systemic therapy and/or developing metastases and/or dying of PCa during the course of study.
4. To determine the proportion of men without any PCa on any post treatment prostate biopsy.
5. To determine the proportion of men with normal baseline serum testosterone who had testosterone recovery (defined as testosterone levels >300 ng/dL) at 6-, 9- and 12-months after FT.

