## Secondary Objectives

1. To assess the genitourinary side effect profile of the combination treatment of androgen deprivation therapy, and partial ablation of the prostate as it pertains to lower urinary tract symptoms and sexual function based on health-related quality of life measures.

1. To determine the prostate specific antigen response following treatment with androgen deprivation therapy, and partial ablation of the prostate.
2. To determine the proportion of men converting to whole gland therapy (radical prostatectomy or radiation therapy) and/or requiring systemic therapy and/or developing metastases and/or dying of prostate cancer during the course of study.
3. To determine the proportion of men with absence of any cancer in the ablated or unablated prostate tissue on post treatment prostate biopsy.
4. To determine the proportion of men with baseline normal serum testosterone who have achieved testosterone recovery over the course of the study and follow-up period.

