**The following principles will dictate the ablation template**:

The treatment or ablation zone will cover the area of the gland in which the CSPCa lesion(s) (GG ≥2) have been identified by the subject's MRI-TB study as follows:

1. A maximum of 60-75% prostate ablation to include all CSPCa. If the patient has more than one focal lesion on one side, all CSPCa lesions will be destroyed.
2. Treatment may reach the urethra and may cross the midline anteriorly or posteriorly.
3. At least one neurovascular bundle must be avoided by ensuring a minimum distance of ablation zone border to the contralateral neurovascular bundle of 5 mm. If ablation of CSPCa cannot be done without damaging both neurovascular bundles, the patient will not be considered for FT.
4. Up to one redo FT treatment is permissible; if either the protocol’s 6-month MRI-TB result(s) of ablated/treated prostate tissue, or a ‘for-cause’ prostate biopsy (see [section 8.7](#_For_Cause_Tests)) are positive at any point in follow-up.

**The following diagrams illustrate some possible interventions using focal therapy: In each of these scenarios below contralateral nerves were spared.**

[figure not shown]

[figure not shown]

[figure not shown]

[figure not shown]

[figure not shown]

[figure not shown]

[figure not shown]

[figure not shown]

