## Post-Focal Therapy Treatment Efficacy/Surveillance mpMRI and MRI-TB

At 12-months from the time of FT, a SOC mpMRI and MRI-TB will be performed to determine treatment response. Both the imaging study and prostate biopsy results will be used to measure efficacy of the proposed combination treatment. However, if a patient has any other post-treatment biopsy results these may also be used to assess for post-treatment efficacy even if not performed with an mpMRI guided biopsy.

Specifically, an MRI-TB will sample the ablated and unablated prostate tissue to determine if residual CSPCa (GG ≥2) remains in the treated and/or untreated prostate tissue. The mpMRI used for the MRI-TB will follow the same imaging protocol as the pre-treatment study and reported in the same manner. Documentation of the biopsy site(s) will be required. If a new suspicious radiographic lesion(s) is/are detected on the subject’s 12-month mpMRI which was/were not present in the pre-treatment [screening] mpMRI then the targeted biopsy cores of the suspicious area(s) will be obtained. Otherwise, if no suspicious lesions are noted in the 12-month mpMRI then random biopsies from the unablated prostate tissue will be obtained per SOC during the MRI-TB.

- Two 18-gauge biopsy cores will be collected from the ablated area(s) and one each from periablation zone and untreated prostate for biobanking and exploratory outcomes on correlatives.

If the 12-month MRI-TB identifies the presence of CSPCa in the ablated or unablated prostate tissue then the patient will be offered a second treatment with FT (if eligible for such treatments) and the follow-up visits for the re-treatment will be the same as the primary treatment. The patients will stay in the study and will continue to be followed up until 12-months from the first FT procedure. For patients with residual/recurrent cancer who decline or are ineligible for a second FT procedure, one of the whole gland treatments, either radical prostatectomy, whole gland ablation or radiation therapy, will be offered. These data will be recorded as part of report of secondary outcomes. Patients who choose to undergo whole gland treatment during the study follow-up will exit the study at this point. HRQOL surveys, PSA and testosterone levels will be obtained at the exit.

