**Descriptive tables as shown below will be populated:**

| **Baseline characteristics** |
| --- |
| Age (years), mean (SD, range) |
| Serum PSA (ng/ml), mean (SD, range) |
| Race |
| Reason for PSA test and Biopsy, % (n)  PSA screening (patient request)  Lower urinary tract symptoms |
| Prostate Volume (mL), mean (SD, range) |
| PSA Density (ng/mL^2^), mean (SD, range) |
| Grade group score on MRI-TB, % (N)  3+4  4+3 |
| MRI-TB, mean (SD, range)  Total Cores  Total Positive Cores  % Positive Cores |
| Risk category (%, n)  Unfavorable intermediate-risk |

| **Peri-operative characteristics** |
| --- |
| Procedure time (minutes), mean (SD, range) |
| Procedure type: HIFU or Cryoablation |
| Discharge time from procedure end (hours), mean (SD, range) |
| Length of catheterization (days), mean (SD, range) # |
| Dysuria (negative urine culture), % (n)  Duration (days), mean (SD, range) |
| Intermittent hematuria (start of stream only), % (n)  Duration (days), mean (SD, range) |
| Urinary debris, % (n)  Duration (days), mean (SD, range) |
| Urinary tract infection (positive urine culture) (%, n) |
| Stricture (%, n) |
| Recto-urethral fistula (%, n) |

| **Histological characteristics at 12-months MRI-TB** |
| --- |
| Number of cores taken, mean (SD, range) |
| PSA density (ng/mL^2^), mean (SD, range) |
| Absence of any cancer (%, n) |
| Absence of Gleason pattern 4 (%, n) |

The primary objective will be expressed as proportions of total number of patients and the 95% confidence interval of the proportion will be presented. Number and grade of complications will be reported.

HrQOL measures collected at 6- and 12-months will be compared to baseline measures using paired tests. In addition, the 6-month and 12-month change from baseline will also be tabulated

PSA: The mean PSA levels at each visit, the overall percent reduction in PSA levels from baseline to each visit, and the proportion of subjects with a PSA reduction compared to baseline at each visit will be presented. Mean PSA nadir and post-nadir PSA values through 12-months post-treatment will be summarized.

Testosterone recovery: Number of men who have recovered normal serum testosterone levels will be expressed as proportions of total number of eugonadal patients and the 95% confidence interval of the proportion will be presented.

Secondary or Adjuvant Treatment: The number and proportion of subjects undergoing secondary treatment during the study will be presented.

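### Secondary endpoint 3 counts only prostatectomy and radiation as whole gland conversion, but the protocol's own follow-up section names whole gland ablation as a third such treatment

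*Protocol*

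**What the plan says.** Three places in the protocol bear on what counts as conversion to whole gland therapy.

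- **Study Design/Endpoints**, secondary endpoint 3: "To determine the proportion of men converting to whole gland therapy (radical prostatectomy or radiation therapy". The parenthesis closes there. Systemic therapy, metastasis and prostate cancer death follow as the other components.
- **Secondary Objectives** has the same construction: "converting to whole gland therapy (radical prostatectomy or radiation therapy) and/or requiring systemic therapy and/or developing metastases".
- **Post-Focal Therapy Treatment Efficacy/Surveillance mpMRI and MRI-TB**, for men with residual or recurrent cancer who decline or cannot have a second focal treatment: "one of the whole gland treatments, either radical prostatectomy, whole gland ablation or radiation therapy, will be offered". It continues "These data will be recorded as part of report of secondary outcomes", and then "Patients who choose to undergo whole gland treatment during the study follow-up will exit the study at this point".

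The analysis section adds a general tally under Secondary or Adjuvant Treatment: "The number and proportion of subjects undergoing secondary treatment during the study will be presented". It does not define secondary treatment or tie it to endpoint 3.

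**The concern.** The endpoint and the conduct section define the same category differently. Neither the endpoint nor the objective has an 'e.g.' or 'including' that would let the parenthesis be read as examples. Taken as written, the protocol recognises three whole gland treatments, sends all three to the secondary outcomes, removes the man from the study for any of them, and then counts two.

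At stake is a small ambiguity that works in one direction. Leaving out a conversion can only lower the reported proportion, which flatters the combination. Two analysts could follow two different sections and report different figures, and the choice might be made after the data are seen. Comparison with outside data is also affected. The 160-man cryoablation series described in the Background defined treatment failure to include any radical or whole gland treatment, without restricting the modality.

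**Working it through.** **1. The definitions side by side.**

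| Place | Prostatectomy | Radiation | Whole gland ablation |
|---|---|---|---|
| Secondary Objectives | yes | yes | not listed |
| Study Design/Endpoints, endpoint 3 | yes | yes | not listed |
| Post-focal-therapy surveillance section | yes | yes | yes |

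The endpoint names two of the three whole gland modalities that the protocol offers.

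**2. Could whole gland ablation be counted as repeat focal therapy instead?** No. The ablation-template principles set "A maximum of 60-75% prostate ablation to include all CSPCa" for focal treatment, and the surveillance section offers whole gland treatment to men who decline or are ineligible for a second focal procedure. The two are separate categories.

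**3. Would another component of endpoint 3 catch the man?** Only if he also had systemic therapy, metastasis or prostate cancer death. If one of these occurred before exit, he is counted anyway. After exit it would generally not be seen: the section specifies quality-of-life surveys, PSA and testosterone at exit and nothing later.

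**4. Would he be reported anywhere?** Probably. The surveillance section has these data recorded with the secondary outcomes, the calendar's long-term follow-up footnote collects re-treatment, and the secondary-treatment tally would ordinarily include him. But that tally is undefined and could also include repeat focal therapy, so it does not give the endpoint 3 proportion.

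**5. Size.** The protocol states no expected value for endpoint 3, so there is no figure to reproduce. The denominator is the planned enrolment: 51 / (1 - 0.10) = 56.7, rounded up to the stated 57.

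- One omitted man: 1/57 = 1.8 percentage points (1/51 = 2.0 points if only 51 are evaluable).
- The protocol gives no rate of whole gland ablation, so the number of such men is an assumption:

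| Assumed men whose only event is whole gland ablation | Understatement, of 57 |
|---|---|
| 0 | 0 |
| 1 | 1.8 points |
| 3 | 3/57 = 5.3 points |
| 5 | 5/57 = 8.8 points |

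**6. Which end of that range is plausible?** Two features point to the low end. Men with clinically significant cancer on the 12-month biopsy are first offered a second focal treatment, so only a subset reaches the whole gland offer. Endpoint 3 also counts events during the study. The calendar places the protocol biopsy at 1 year (window of 4 weeks either side), while follow-up ends 1 year after focal therapy, so many treatments prompted by that biopsy would come after the window closes. For-cause biopsies can lead to earlier conversions. A few sections still mention a 6-month MRI-targeted biopsy, but the calendar's MRI-TB row schedules it only at 1 year.

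**The case against.** The strongest reply is that nothing is lost. The surveillance section records these men with the secondary outcomes, and the analysis section presents the number and proportion having secondary treatment. This stands as far as it goes. A reader might infer that whole gland ablations go unreported, and the protocol does not support that. What remains open is whether they belong in the endpoint 3 composite, and an undefined tally does not settle it.

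It can also be said that the omission may be deliberate, with only surgery and radiation meant to count as conversion. The documents do not show which was intended. That affects how to fix the mismatch, not whether it exists.

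Two stronger readings are tempting and should be resisted.

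- **A shortfall of 5 to 10 points.** One could apply the planning proportions of 15% and 30% to 57 men (8.55 and 17.1 biopsy-positive), assume that one third have whole gland ablation (2.9 and 5.7 men), and arrive at 5 to 10 points. The one-third share has no source in the protocol. The calculation also skips the second focal treatment offered first, and it treats every positive man as converting within a window that closes at about the time of the biopsy.
- **Bias between sites.** One might suppose that ablation-experienced centres would be understated most. The protocol plans no between-site comparison, lists no stratification factors, requires experienced surgeons for focal therapy at their respective institutions, and nowhere links site to the choice of later treatment.

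**Conclusion.** The inconsistency is real and appears in both the objective and the endpoint. Read literally, endpoint 3 omits a conversion that the protocol itself recognises, and the omission can only lower the proportion. The supportable size is 1.8 percentage points per man at N = 57. The number of men is unknown and may be zero or small. This assumes that the man has no other endpoint 3 event and that the parenthesis is applied as written.

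The consequence is limited. The endpoint is secondary and descriptive, with no hypothesis, threshold or role in the sample size. The primary biopsy and safety endpoints, the 51 evaluable men and the total of 57 are unaffected.

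**What to change.** Use one outcome definition in Secondary Objectives, Study Design/Endpoints and the post-focal-therapy surveillance section. There are two acceptable ways:

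1. Count whole gland ablation, by changing the parenthesis in the objective and in endpoint 3 to *(radical prostatectomy, radiation therapy or whole gland ablation)*.
2. If its exclusion is intended, say so in both places and report whole gland ablation as a separate line beside endpoint 3.

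Either way, settle it before conversions are tabulated. The cost is a few words in two places. Only outcome counting changes: no treatment choice, sample size or primary analysis is touched.

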## Sample Size/Accrual Rate

It is estimated that the 30% of men who undergo FT for intermediate-risk PCa will have CSPCa (GG ≥2) on repeat biopsy after FT. We hypothesize the combination of ADT, and FT will halve the proportion of men with residual or recurrent CSPCa to 15%. Using sample size estimates for a single proportion, comparing a null proportion of 0.30 to an alternative proportion of 0.15, with an alpha = 0.05 and power at least 80%, the total number of patients required will be 51 men. We estimate 10% attrition for a total sample size of 57 men. We are expecting 18-21 months to enroll all the patients and 36-months to complete the study.

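### The stated power of at least 80% with 51 men holds only under an unstated one-sided normal approximation; true power is about 77%, and lower if an exact or Wilson 95% CI is the yardstick

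*Protocol*

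**What the plan says.** Section 13.4 (Sample Size/Accrual Rate) hypothesises that adding ADT to focal therapy "will halve the proportion of men with residual or recurrent CSPCa to 15"%, from an expected 30%. The calculation is described as "Using sample size estimates for a single proportion", "comparing a null proportion of 0.30 to an alternative proportion of 0.15", and concludes: "with an alpha = 0.05 and power at least 80%, the total number of patients required will be 51 men". It then adds: "We estimate 10% attrition for a total sample size of 57 men". No sidedness, named test or success threshold is given.

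Section 13.6 (Analysis of Primary and Secondary Endpoints) gives the planned readout: "The primary objective will be expressed as proportions of total number of patients and the 95% confidence interval of the proportion will be presented". It names no interval method and no comparison of the interval with 0.30. Under Missing Data, the same section imputes treated men without a post-ablation biopsy as positive in the primary analysis.

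**The concern.** The power statement and the planned readout are not visibly connected. If alpha is two-sided, 51 men are too few. If it is one-sided, the number roughly fits, but a conventional 95% interval corresponds to one-sided 2.5%, a stricter level than the one that produced 51.

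This is a single-arm trial with one fixed benchmark. A plausible count such as 9 of 51 can therefore be called a success or a failure depending on a choice the protocol leaves open, and that choice should not be available after the data are seen. The phrase used is also at least 80%, so it matters whether the stated number of men actually delivers 80%.

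**Working it through.** **Inputs** (Section 13.4): p0 = 0.30, p1 = 0.15, alpha = 0.05, power 0.80, n = 51, attrition 10%. Variances: p0(1 − p0) = 0.21; p1(1 − p1) = 0.1275.

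**Step 1. Reproduce the plan's figure.** The standard one-sample formula is n = [(z_alpha·√0.21 + 0.8416·√0.1275) / 0.15]².

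- One-sided 5% (z = 1.645): n = 49.4, so 50.
- Two-sided 5% (z = 1.960): n = 63.9, so 64.

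The power at 51 from the same approximation is Φ[(0.15·√51 − z_alpha·√0.21) / √0.1275]: 81.3% one-sided and 68.6% two-sided. Attrition: 51/0.9 = 56.7, so 57, as stated.

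Other common formulas come no closer to 51:

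| Formula | One-sided | Two-sided |
| --- | --- | --- |
| Continuity-corrected | 56 | 71 |
| Arcsine | 47 | 60 |
| Wald, variance at p1 | 36 | 45 |
| Wald, variance at p0 | 58 | 74 |

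The one-sided normal approximation is the nearest match, within one patient.

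**Step 2. True power of that one-sided test at n = 51.** The z statistic is (x/51 − 0.30)/√(0.21/51). For x = 9 it is −1.93, which rejects at −1.645. For x = 10 it is −1.62, which does not. The exact binomial test has the same cutoff.

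- Size: P(X ≤ 9 | 0.30) = 3.4%. One more positive would give 6.7%.
- Power: P(X ≤ 9 | 0.15) = 77.3%.

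**Step 3. The 95% interval as yardstick at n = 51.** Upper limits:

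| Positives | Clopper-Pearson | Wilson | Wald |
| --- | --- | --- | --- |
| 8 | 28.6% | 28.0% | 25.7% |
| 9 | 30.9% | 30.3% | 28.1% |
| 10 | 33.1% | 32.5% | 30.5% |

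Clopper-Pearson and Wilson limits exclude 30% at 8 or fewer: size 1.5%, power 64.6%. Wald limits exclude it at 9 or fewer: power 77.3%. At 9 of 51 the one-sided 5% test rejects, while the Clopper-Pearson and Wilson intervals still contain 30%.

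**Step 4. All 57 men in the analysis.** With every biopsy available:

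- One-sided 5%: 11 or fewer, size 4.9%, power 86.2%.
- Clopper-Pearson or Wilson 95% interval: 10 or fewer, size 2.4%, power 77.2%.

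Section 13.6 counts a missing biopsy as positive. With m missing out of 57, the one-sided rule therefore allows only 11 − m positives among 57 − m biopsied men:

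| Missing biopsies | Rule among biopsied men | Power |
| --- | --- | --- |
| 0 | ≤ 11 of 57 | 86.2% |
| 2 | ≤ 9 of 55 | 69.4% |
| 6 (57 − 51) | ≤ 5 of 51 | 20.3% |

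**The case against.** The best defence is that the protocol never says two-sided. The hypothesis is directional, one-sided 5% is an ordinary choice in a single-arm phase I/II trial, and under it the textbook formula gives 50 men and 81.3% nominal power at 51. That stands, and it means the number is not a slip of arithmetic.

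A reader might go further and infer that the trial has only about 65% power, because its conclusion will rest on whether the 95% interval excludes 30%. The documents do not support that. Section 13.6 says only that the interval will be presented, and no section makes it the success rule. The 65% also depends on an interval method that is not named; Wald limits share the cutoff of the one-sided test at both 51 and 57.

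It is also fair that the shortfall to 77.3% partly reflects binomial discreteness: the same exact test reaches 80.9% at 49 men and 83.8% at 53. The shortfall still applies at the number the protocol states.

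Finally, the test, the threshold and the interval method may be set out in an analysis plan not shown here. Their absence alone would not be a finding. What remains is a numerical claim in the protocol itself, at least 80% power with 51 men, that the binomial calculation does not bear out.

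**Conclusion.** The concern holds in a limited form. The power statement rests on an unstated one-sided 5% normal approximation. The true power of that test at 51 men is 77.3%, a shortfall of about 3 points. If the planned 95% interval were used against the 30% null, power at 51 would be 64.6% (Clopper-Pearson or Wilson) or 77.3% (Wald). The two-sided normal approximation gives 68.6% and would need 64 men. None of the binomial-based criteria checked at 51 reaches 80%.

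These figures assume a true rate of 15%, a fixed benchmark of 30% and 51 men in the analysis. They do not show that the power is grossly wrong under every reading, or that the trial must be enlarged. This should be fixed, but it does not invalidate the design.

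**What to change.** Choose one of two routes and write it into Sections 13.4 and 13.6.

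1. State that 0.30 is tested with a one-sided exact binomial test at 5%, with success at 9 or fewer positives of 51. Report a 90% interval or a one-sided 95% upper bound so that the interval agrees with the test. Restate power as about 77% at 51 evaluable men.
2. Keep the 95% interval as the criterion, name its method, and restate power as about 65% at 51 for exact or Wilson limits.

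Under either route, quote power for 57 men (86% one-sided; 77% for the exact 95% interval) only as the value with no missing biopsies, because imputation as positive lowers it quickly. Say also that imputed positives count towards the threshold.

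The cost is about two sentences and a slightly less favourable power figure. Enrolment is unchanged.
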